### 5.3.1 Niger

#### 5.3.1.1 BACKGROUND

In Niger, all procedures and protocols must be approved by the National Ethics Committee. The National Ethics Committee has requested oral consent for all participants, following a standard protocol within the grappes. This study involves a random selection of children and adults, who will be screened for clinical trachoma and have a swab taken of the upper eye lid to determine presence of infection. In addition, a random sample of children will receive nasopharyngeal swabbing to test for pneumococcal resistance. All persons in participating grappes will have the opportunity to be treated according to their community's treatment assignment. Grappes not included in one of the study arms will still be offered treatment through the national treatment program.

#### 5.3.1.2 CONSENT PROCEDURES

Several levels of recruitment are involved when working in Niger. At grappe level, our research team discusses the project with the village chief. Once leadership consents to participation, we will undertake a complete census of study areas by going house to house in each grappe (see Chapter 6). At this second level, we ask permission of the head of the household or an adult dwelling in the household to collect data on household characteristics and the age and gender of each resident of the household. At this time, we explain the following: the census will be used to monitor the uptake of mass treatment in the community and to draw a random sample of children ages 0-5. These children may be eligible to be in the surveys that will be done at baseline, and every six months after mass treatment. At this point we describe what the survey entails (trachoma assessment of the child, and a swab taken of the upper eye lid to detect Chlamydia, the bug that causes trachoma). We ask them to consider that, if the household contains a child of eligible age who is selected, we will return to seek permission to examine the child.

Our local team members will provide information and seek consent, as they are fluent in Hausa, the local language in the Matameye district. The Nigerien study coordinator will train the team in research ethics and informed consent. The team will explain that the purpose of the project is to determine severity of trachoma and infection before and after treatment by examining a sample of the children in the grappe. They will demonstrate the use of the swab and explain that participation is completely voluntary and will not affect access to health care or access to the mass treatment to come after the survey. Additionally, they will explain that different grappes will receive different treatments in an effort to determine the best treatment, and that treatment for trachoma will be provided to everyone in the grappe once examinations are completed. If a child is selected for a nasopharyngeal swab, another consent will be obtained, using similar procedures explained above. If the participant or the participant's guardian agrees to participate, they will mark a fingerprint on the consent form. All consent forms will be kept by PNLCC in Niamey.

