### 1.3 Overall Design

We propose a community-randomized design within each of the three countries, which takes advantage of the level of endemicity to address questions of coverage and frequency. Within these study areas, communities will be randomized (minimum 16 in each arm) to two different coverage targets (80%-89% versus  $\geq 90\%$ ) for three years of mass treatment. In Niger, we will further randomize communities to annual mass azithromycin distribution versus every 6-month distribution. Only children ages 12 and under will receive azithromycin treatment. In The Gambia and Tanzania, we will further randomize communities to yearly mass treatment versus annual mass treatment if warranted by the trachoma infection rates. We will evaluate the efficacy of guiding further mass treatment according to a laboratory test for Chlamydia or WHO guidelines. Where we estimate communities have infection rates less than 5% in sentinel children, or TF rates less than 5%, the community will be “graduated” from further mass treatment and followed for up to three years to look for evidence of re-emergent infection and disease. If rates of infection return to 20% at the 12 or 18-month survey, we will initiate mass treatment again.

Sentinel children randomly selected as cross sectional samples in these communities will be monitored at baseline, 6, 12, 18, 24, 30, and 36 months for infection and clinical disease. The three-year study is in accord with the WHO guidelines for three years of mass treatment followed by a re-survey to determine areas in need of further treatment.

Primary analyses will focus, within countries, on the comparison at three years of trachoma and infection rates in villages randomized to 90% or greater coverage versus less than 90%, and in villages randomized to yearly treatment of everyone versus 6 monthly treatment of children (Niger) or yearly versus in the “stopping rule” arm (Tanzania and The Gambia). Primary analyses will consider the 2 X 2 factorial design, the baseline prevalence, and baseline indicators of environmental hygiene as co-variables and effect modifiers. Secondary analyses will evaluate trachoma and infection in children, adjusting for clustering at the village level.

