We plan to have our local team members provide the information and seek consent, as they are fluent in Swahili and the local language for Kongwa, Chigogo. [name] will train the team using the Johns Hopkins IRB course in research ethics and informed consent. The team will explain that the purpose of the project is to determine rates of trachoma and infection before and after treatment in this village, by examining a sample of the children in the village. They will demonstrate the use of the swab, and explain that participation of the child is completely voluntary and will not affect access to health care, or access to the mass treatment to come after the survey. They will explain that treatment for trachoma will be provided after the research survey is completed, to everyone in the village, but the family will be told the results of the examination. He will explain the project to the parents in the presence of the child, and show him/her what the examination entails. However, the parent is the decision maker as children age five (or even nine) and under have not yet gone through ceremonies for passage to adult hood and therefore will not countermand adult authority-asking them is a courtesy but rarely will an answer be obtained that is different.

Once the sample is drawn, our team will approach the child's mother or father directly to seek verbal consent for participation in the survey. We have always sought verbal consent for our studies in the rural villages of Tanzania. Most people are functionally illiterate and are asked to sign their names for taxes, collection of money, or more sinister schemes where their land has been taken away. We consider it unethical to have them sign a piece of paper they cannot read, and have always requested approval to obtain witnessed verbal consent.

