Procedures for protection against risk include the following: we are careful to have a single individual flip the lid while the senior lab technician carries out the examination, takes the swab, and the photograph of the upper eye lid. In this way, any psychological trauma to the child, or discomfort from having the eyelid flipped is minimized as the lab technician can work quickly. In addition, by having the person hold the eyelid, the swab procedure can be done safely without worry of accidental corneal scratch. We have never had an accident in all the years we have taken swabs for trachoma using these procedures. In the unlikely event of a corneal scratch, the team has an eye patch and topical tetracycline and can treat the scratch immediately. We will minimize any inadvertent transmission from one child to another by having all persons who touch the eyelid change gloves between each child. In the unlikely event that infection is transmitted, the mass treatment offered after our survey should eliminate any infection. The results of the examination are told to the parents immediately after the examination, and not revealed to other members of the village.

The forms are stored in a folder, which after data entry are kept in a locked file room. The data are transmitted to the main data centers without names, just identification numbers. Such procedures ensure confidentiality.

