For villages that meet the stopping rule, mass treatment will be stopped after the survey in which criteria was met. Theoretically, then a community may receive one round of mass treatment, and not again until after the third survey. If infection is subsequently found in any of the sentinel children, the child may not receive azithromycin until after the third survey. We have previously received ethical approval to conduct longitudinal surveys in these communities following mass treatment, without re-treatment. Because the infection is largely self limited and does resolve, by the time the PCR was completed and results known, the child would likely have no infection when we returned. If these communities have had no infection post treatment, which made them eligible for the stopping rule, the likelihood of experiencing repeated bouts of infection is remote. The risk of scarring takes at least five years with repeated bouts of infection, which under the conditions of the stopping rule, will be rare. In addition, the parents may seek tetracycline eye ointment which is kept at the health post or health centers as part of the essential drug kit.

---

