| Arm D Grappes 37-48               | Months 0-2      | Months 0-2                         | Months 6-8     | Months 6-8                         | Months 12-14    | Months 12-14                       | Months 18-20    | Months 18-20                       | Months 24-26    | Months 24-26                       | Months 30-32     | Months 30-32                       | Months 36-38    |

Note: Arms C and D only treat children ages 0-12. A and B are the annual treatment arms. C and D are the biannual treatment arms.

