Once a community has been stopped, it will not receive mass treatment again until after the third year survey, unless the 12 or 18 month survey show infection has climbed back to 20%, in which case mass treatment will be reinstituted at the next round. This parallels the WHO rule of re-surveying at three years to determine if further treatment is necessary. For example, if a community has no infection, as determined in the sentinel children, after the first round of mass treatment, the community will not receive mass treatment at the second or third rounds, even if infection starts to rebound, unless it rebounds to 20% by the 12 or 18 month survey. In this way, we are able to

determine if, or with what rapidity, infection re-emerges. All communities will receive mass treatment after the last survey at three years, post baseline.

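### Consent descriptions for Niger and Tanzania, and the risk section, say mass treatment of everyone follows the examination, but after several surveys no round is scheduled, and in half of Niger's grappes the rounds leave out residents over 12

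*Protocol*

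**What the plan says.** **Consent.** In Niger (5.3.1.2) the team explains that "different grappes will receive different treatments in an effort to determine the best treatment" and, in the same sentence, that "treatment for trachoma will be provided to everyone in the grappe once examinations are completed". In Tanzania (5.3.2.2): "They will explain that treatment for trachoma will be provided after the research survey is completed, to everyone in the village". Section 7.2 has the intake clerk carry out the section 5.3 consent at the examination visit, and section 7.5 applies the baseline procedures unchanged to every later visit.

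**Risk.** Section 5.4 calls transmission between children during examination a theoretical risk that handling procedures make very small. It then adds: "In the unlikely event that infection is transmitted, the mass treatment offered after our survey should eliminate any infection". For stopped communities the same section says: "If infection is subsequently found in any of the sentinel children, the child may not receive azithromycin until after the third survey".

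**Schedule.** Sentinel children "will be monitored at baseline, 6, 12, 18, 24, 30, and 36 months for infection and clinical disease" (1.3). Tables 2 and 3 in section 7.6 place the yearly rounds after the baseline, 12- and 24-month surveys. On Niger, the text under Table 3 reads: "Note: Arms C and D only treat children ages 0-12". Section 8.6 (Tanzania and The Gambia) says: "Once a community has been stopped, it will not receive mass treatment again until after the third year survey". It makes an exception if infection is back at 20% at the 12- or 18-month survey, and adds that all communities are treated after the three-year survey.

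**The concern.** A guardian or adult who hears the described explanation at, say, the 6-month survey would expect the whole community to be treated next. In a yearly arm no round is due for six months. In a stopped community it may be much longer. An adult in a Niger child-treated grappe is in no scheduled round at all. Followed as written, the plan gives some participants a statement that is untrue for them. Part of the risk assessment in 5.4 rests on the same premise, so an ethics committee would be relying on a remedy that the schedule does not always supply.

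**Working it through.** The protocol gives no figure of its own on this point, so there is none to reproduce. The check sets surveys against treatment rounds.

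**Inputs**
- Surveys at months 0, 6, 12, 18, 24, 30 and 36, seven in all (1.3, 4.1).
- Yearly rounds after months 0, 12 and 24 (Tables 2 and 3).
- A round after month 36 for all communities (8.6). This sentence stands in a section on Tanzania and The Gambia, and Table 3 lists no such round for Niger.
- A community stopped after the 6-month survey misses rounds two and three unless the 20% restart applies (8.6).
- Niger arms C and D: 24 of 48 grappes, treatment for ages 0-12 only (Table 3, 8.2.1), with 40 adults aged 15 or over sampled per grappe at each collection (4.3.1). The Niger consent background (5.3.1.1) says that selected adults are screened and swabbed.

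**Surveys with no round after them = 7 minus surveys followed by a round**

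| Setting | Round follows survey at month | None follows month | Count |
|---|---|---|---|
| Yearly arm, with the post-36 round | 0, 12, 24, 36 | 6, 18, 30 | 3 of 7 |
| Niger yearly arm, Table 3 alone | 0, 12, 24 | 6, 18, 30, 36 | 4 of 7 |
| Stopped after month 6, no restart, with post-36 round | 0, 36 | 6, 12, 18, 24, 30 | 5 of 7 |
| Same, restart gives a round at month 24 | 0, 24, 36 | 6, 12, 18, 30 | 4 of 7 |
| Niger arms C and D, residents over 12, Table 3 | none | all | 7 of 7 |
| Same, if the post-36 round covers Niger and all ages | 36 | 0, 6, 12, 18, 24, 30 | 6 of 7 |

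**People affected**
- Niger adults examined in arms C and D: 24 x 40 = 960 per round at most.
- Tanzania: no arm has a round after months 6, 18 or 30. At the planned 3,200 children per survey (7.2.5), that is 3 x 3,200 = 9,600 planned examinations whose consent description does not fit the schedule.
- Stopping is not a remote case. Section 4.4.1 expects 40% to 80% of stopping-rule communities to stop after one or two rounds. For Tanzania's 16 that is 6.4 to 12.8, or about 6 to 13. Not all of these would stop as early as month 6, so 5 of 7 applies only to those that do.

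**The case against.** **What the protocol discloses elsewhere.** Section 5.3.1.1 says people are treated according to their community's assignment, and section 7.5 ties treatment to the arm. Section 5.4 openly says that an infected child in a stopped community may go untreated, and gives reasons. Sections 8.2 and 8.2.1 have health workers answer questions about the age limit, and section 8.3 has the supervisor explain an unusual assignment to village leaders. Niger families are told that treatments differ between grappes. All this softens the conflict. It does not remove it: the individual consent descriptions do not pass these limits on, and the Niger sentence that mentions different treatments goes on to promise treatment to everyone.

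**What cannot be seen.** The consent forms and The Gambia's information sheet are not shown. The point therefore concerns the procedures as the protocol describes them for Niger and Tanzania, and makes no claim about The Gambia's text.

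**Stronger readings that the document does not support**
- A reader might infer that mass treatment is the main protection against transmission. In 5.4 the main protection is handling and glove changes. Treatment is a fallback.
- A reader might count the third survey in 5.4 as month 12 and see a conflict of 24 months with the third-year survey in 8.6. That count makes the sentence pointless. Round two falls directly after the 12-month survey, so a community treated then would have missed nothing. Only the third-year reading makes sense, and the difference is one of wording.
- A reader might infer that Niger residents over 12 in arms C and D are never treated. That holds for the rounds in Table 3. If the closing sentence of 8.6 covers Niger and all ages, they could be reached after month 36.
- A reader might expect untreated adults to seek azithromycin elsewhere and so dilute the children-only comparison. Nothing in the document shows this, and no size can be given.

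**Conclusion.** The conflict is real and lies in the text. As described for Niger and Tanzania, consent at every survey includes a statement that treatment of everyone follows. For yearly arms this fails after at least 3 of 7 surveys (4 of 7 for Niger by Table 3 alone). For a Tanzanian community stopped after month 6 it fails after 5 of 7, assuming that no restart is triggered and that the post-36 round takes place. For residents over 12 in Niger arms C and D it fails at every scheduled round, with up to 960 examined adults per round. The remedy offered in 5.4 fails wherever no round follows or the person is outside the treated ages.

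This is a matter of accurate consent and risk statements. It does not bias the outcome comparison in any way the document demonstrates. The text should be corrected, because as written it would be untrue for identifiable groups at identifiable visits.

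**What to change.** 1. Reconcile 5.3.1.2, 5.3.2.2 and 5.4 with 7.5, Tables 2 and 3, 8.2.1 and 8.6.
2. Reword the oral explanation as one text used in all arms. It should say that, depending on the community's assignment and the survey, treatment may not follow this visit, and that in some Niger communities it covers only ages 0-12. A script that named the arm would undo the masking of survey teams that 8.7 and 10.7 try to keep.
3. In 5.4, limit the statement that later treatment removes transmitted infection to the surveys and people for whom a round follows.
4. Align the survey named in 5.4 for stopped communities with the third-year survey in 8.6, as a wording correction.
5. State whether the treatment after the last survey in 8.6 also applies to Niger and to which ages, so that Table 3 and 8.6 can be read together.

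Which treatment rule applies is for the sponsor and the ethics committees. The cost is revised text and oral scripts, with an ethics notification in each country concerned. Sample size, schedule of surveys and analysis stay as they are.

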### 5.3.2 Tanzania

#### 5.3.2.1 BACKGROUND

In Tanzania, all procedures and protocols go through the National Institute for Medical Research for Institutional Review Board approval within the country. In general, when we have submitted research on trachoma to them, we ask for permission to obtain oral consent for all participants, following a standard protocol within the villages. This study involves children, who will be screened for clinical trachoma and have a swab taken of the upper eye lid to determine presence of infection. All persons in the study villages will have the opportunity to be treated with oral azithromycin at baseline, as part of the yearly mass treatment effort in Kongwa district. Half the

villages will also be offered mass treatment with azithromycin yearly over the next three years, and half the villages will be treated only if the sentinel children have no evidence of either infection or TF.

#### 5.3.2.2 CONSENT PROCEDURES

There are several levels of recruitment when working in Tanzania. The first is the level of the community, where our team goes and talks about the project to the community leadership. This information is then imparted throughout the village by a series of village meetings held by the leadership where the research project is discussed and participation is discussed. When our team returns, we must address specific questions the village may have before allowing us entry. While it is rare to have a village refuse to participate, we have had two villages refuse, in 18 years of research.

Once the community leadership consents, we then go house to house to undertake a complete census (see Chapter 6). At this second level, we ask permission of the head of the household or an adult dwelling in the household to collect data on household characteristics, and the age, and gender of each resident of the household. At this time, we explain the following:

- The census will be used to monitor the uptake of mass treatment in the community and to draw a random sample of children ages 0-5 who will represent the children in this community.
- If this household includes children ages 0 to 5 years, these children may be eligible to be in the surveys that will be done at baseline, and every six months after mass treatment.
- Participation in the survey entails trachoma assessment of the child, and a swab taken of the upper eye lid to detect Chlamydia, the bug that causes trachoma.
- We ask them to consider that if the household contains a child of eligible age who is selected, we will return to seek permission to examine the child.

We plan to have our local team members provide the information and seek consent, as they are fluent in Swahili and the local language for Kongwa, Chigogo. [name] will train the team using the Johns Hopkins IRB course in research ethics and informed consent. The team will explain that the purpose of the project is to determine rates of trachoma and infection before and after treatment in this village, by examining a sample of the children in the village. They will demonstrate the use of the swab, and explain that participation of the child is completely voluntary and will not affect access to health care, or access to the mass treatment to come after the survey. They will explain that treatment for trachoma will be provided after the research survey is completed, to everyone in the village, but the family will be told the results of the examination. He will explain the project to the parents in the presence of the child, and show him/her what the examination entails. However, the parent is the decision maker as children age five (or even nine) and under have not yet gone through ceremonies for passage to adult hood and therefore will not countermand adult authority-asking them is a courtesy but rarely will an answer be obtained that is different.

Once the sample is drawn, our team will approach the child's mother or father directly to seek verbal consent for participation in the survey. We have always sought verbal consent for our studies in the rural villages of Tanzania. Most people are functionally illiterate and are asked to sign their names for taxes, collection of money, or more sinister schemes where their land has been taken away. We consider it unethical to have them sign a piece of paper they cannot read, and have always requested approval to obtain witnessed verbal consent.

